### Interventional treatment

In the study group, at the end of the induction of general anesthesia, a bolus of 1.5 mg.kg^− 1^ of intravenous lidocaine will be administered, followed by a continuous infusion of intravenous lidocaine at 2 mg.kg^− 1^.h^− 1^. The lidocaine infusion will be reduced to 1 mg.kg^− 1^.h^− 1^ in the postanesthesia care unit (PACU) and will be discontinued at the time of discharge. The placebo group will receive, in the perioperative period, a placebo infusion with 5% glucose solution at a rate comparable to that of the lidocaine infusion in the study group.

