### Secondary outcome

Secondary outcomes include: cumulative remifentanil consumption during surgery; cumulative morphine consumption in the first 24 postoperative hours; assessment of CPSP 3–6 months after surgery using the shortened version of the QDSA; and occurrence of adverse events.

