### Data analysis

Data will be analyzed according to the intention-to-treat principle. Unblinding is planned at the end of the study, after a database freeze. A descriptive analysis will first be performed. The data will be presented as counts and percentages for qualitative data, as means and standard deviation for normally distributed quantitative data, or as medians and interquartile range for non-normally distributed variables. The analysis of the main outcome (cumulative morphine consumption in the first 48 postoperative hours) will be performed using Student’s *t* test. A multivariate linear regression analysis will also be performed to identify factors independently associated with morphine consumption 48 h after surgery. The factors studied will be the type of surgery, tumor site, stage of cancer, duration of the surgery, NRS score upon arrival in the PACU, use of preoperative analgesic, and use of high-dose intraoperative remifentanil. During surgery, intraoperative remifentanil consumption as well as morphine consumption in the 24 postoperative hours will be compared between the two groups using Student’s *t* test. The incidence of postoperative chronic pain will be compared between the two groups and the factors potentially associated with the occurrence of chronic pain will be analyzed by logistic regression. Subgroup analysis will be performed to compare patients with and without major pectoralis flap or free flap. The statistical analyses will be carried out under the responsibility of the methodologist of the clinical research center of the Croix-Rousse Hospital. All analyses will be conducted using SPSS software version 19.0 (IBM Corp., Armonk, NY, USA) and R software (R Development Core Team, Vienna, Austria). A value of *p* < 0.05 will be considered statistically significant.

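### The regression for factors independently associated with 48 h morphine omits treatment arm and centre from its list but includes two factors measured under treatment

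*Protocol article*

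**What the plan says.** All references are to the Methods/design part of the protocol article.

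- **Data analysis, primary test.** "The analysis of the main outcome (cumulative morphine consumption in the first 48 postoperative hours) will be performed using" Student's t test, with no adjustment.
- **Data analysis, regression.** "A multivariate linear regression analysis will also be performed to identify factors independently associated with morphine consumption 48 h after surgery". The list that follows is worded as complete. It opens "The factors studied will be the type of surgery, tumor site, stage of cancer, duration of the surgery" and, taken up again from duration, runs "duration of the surgery, NRS score upon arrival in the PACU, use of preoperative analgesic, and use of high-dose intraoperative remifentanil". That makes seven factors. Neither treatment arm nor centre is among them.
- **Interventional treatment.** Lidocaine begins early: "at the end of the induction of general anesthesia, a bolus of" study drug is given, followed by an infusion that continues through surgery and the PACU stay.
- **Secondary outcome.** The first item is "cumulative remifentanil consumption during surgery", which the Data analysis section compares between the arms.
- **Randomization.** Allocation is stratified by centre, with two centres.
- **Postoperative analgesia.** A pain score above 3 in the PACU triggers morphine titration.

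**The concern.** Two of the seven factors, remifentanil use during surgery and pain on PACU arrival, are observed while the patient is receiving lidocaine or placebo. The protocol itself treats remifentanil consumption as something lidocaine may change, because it is a secondary efficacy outcome. Pain on PACU arrival is an early sign of the analgesic effect under test, and it also prompts morphine dosing.

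A model that holds these two factors but not the randomised treatment cannot separate their association with morphine from lidocaine's own effect. If lidocaine patients arrive with less pain and also need less morphine for other reasons, the pain coefficient takes credit for both. The claim of independent association is then not supported.

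A second risk arises if arm is later put into this model without other changes. The arm coefficient would exclude whatever part of the effect passes through PACU pain and remifentanil. It could then be read beside the t test as though both estimated the same quantity. This is the only multivariable analysis of the primary outcome that the article describes.

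**Working it through.** **Inputs from the protocol (Sample size calculation).** Control mean 43 mg; target reduction 20%, so the total effect is 0.20 × 43 = 8.6 mg; 57 per group, 114 in all.

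**Assumed inputs.** The protocol gives no figure for lidocaine's effect on PACU pain or remifentanil, or for their effect on morphine. Three illustrative settings:

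| Setting | Fall in NRS (points) | Morphine per NRS point (mg) | Fall in high-dose remifentanil use | Morphine per high-dose use (mg) |
|---|---|---|---|---|
| A | 0.5 | 2 | 0.10 | 5 |
| B | 1.0 | 3 | 0.20 | 5 |
| C | 1.5 | 3 | 0.20 | 8 |

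**Step 1: split the total effect.** Mediated part = (NRS fall × mg per point) + (remifentanil fall × mg). Direct part = 8.6 − mediated part.

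- A: 0.5 × 2 + 0.10 × 5 = 1.5 mg mediated; 7.1 mg direct.
- B: 1 × 3 + 0.20 × 5 = 4.0 mg mediated; 4.6 mg direct.
- C: 1.5 × 3 + 0.20 × 8 = 6.1 mg mediated; 2.5 mg direct.

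**Step 2: the model as listed, arm omitted.** The shift in a factor's coefficient is the direct effect multiplied by the slope of arm on that factor. Worked for NRS alone in setting B, with an assumed within-arm NRS SD of 2:

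- Arm is 0/1 in equal numbers, so its variance is 0.25. Its covariance with NRS is −1 × 0.25 = −0.25.
- Overall NRS variance is 2² + 1² × 0.25 = 4.25.
- Slope of arm on NRS is −0.25 / 4.25 = −0.0588.
- Shift is (−4.6) × (−0.0588) = 0.27 mg per point. Against a true 3 mg this is 0.27 / 3 = 9%.

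With both factors in the model, within-arm NRS SD from 1.5 to 3 and half of patients on high-dose remifentanil, the same formula in its two-factor form gives:

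| Setting | Inflation of NRS coefficient | Inflation of remifentanil coefficient |
|---|---|---|
| A | 5% to 19% | about 14% |
| B | 4% to 15% | 17% to 18% |
| C | 3% to 11% | 5% to 6% |

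Simulation of the same settings gave 3% to 20% for NRS and 5% to 18% for remifentanil. For scale, take setting B with NRS SD 2, an assumed residual SD of 14 mg and 114 patients. The shifts are 0.26 mg per point and 0.87 mg, against standard errors of about 0.64 and 2.66 mg.

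**Step 3: the variant with arm added and both factors kept.** The arm coefficient estimates the direct part only. The share lost is mediated / 8.6: A 1.5 / 8.6 = 17%; B 4.0 / 8.6 = 47%; C 6.1 / 8.6 = 71%. Simulation of these settings gave 17%, 46% and 72%. These percentages restate the assumptions; they are not evidence about this trial.

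**The case against.** The strongest reply is that the regression is not meant to estimate the lidocaine effect. The unadjusted t test under intention to treat does that. The regression is additional and prognostic, and a prognostic model may properly use intraoperative and PACU information. Including high-dose remifentanil also looks deliberate, since the Background links heavy opioid exposure to hyperalgesia. Finally, a condensed article may simply not mention that arm and centre enter the model.

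Much of this stands:

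- The primary p-value, the sample size and the between-arm comparisons are untouched.
- Such predictors are legitimate in a descriptive model.
- Only lidocaine's direct effect can leak into the two coefficients. If lidocaine acted wholly through them, omitting arm would bias neither.

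What does not stand is leaving the list as it is. It is worded as the set of factors studied, and it names the two treatment-affected factors while leaving out the randomised treatment. A prognostic model for an outcome that the trial drug is expected to change still needs arm in it before any other factor is called independently associated. The omission of arm and centre might be shorthand; the inclusion of the two factors is not, because they are named.

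A reader might go further and infer that the trial will report a lidocaine effect shrunk by a large fraction, or a regression that contradicts the t test. The documents do not support that. As listed, the model has no arm term and so reports no lidocaine effect.

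**Conclusion.** The point holds as a limited defect in a supporting analysis. The listed model cannot support a claim of independent association, because it omits the randomised treatment and the stratification factor while including two factors measured under treatment. Under the assumed values the two coefficients are inflated by roughly 3% to 20%, within one standard error at 114 patients. This rests on assumed mediator effects, NRS spread, residual SD and prevalence of high-dose remifentanil, none of which the protocol gives.

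The larger range of about 17% to 71% belongs only to a variant in which arm is added and both factors stay. Its true size cannot be known from the documents. It is a reason to specify the model carefully, not a forecast. Nothing here calls the primary analysis into question.

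**What to change.** 1. Add treatment arm and centre to the regression on 48 h morphine.
2. For any adjusted estimate of the lidocaine effect, use only arm, centre and factors fixed before randomisation: planned type of surgery, tumour site, stage and preoperative analgesic use. Leave out PACU pain score and high-dose remifentanil. Leave out duration of surgery too, because it is known only after treatment has started; this does not claim that lidocaine changes it.
3. Keep the model with intraoperative and PACU factors as a separate prognostic model. Include arm in it, label it descriptive, and state that it is not used to interpret the lidocaine effect.

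The cost is some wording and one additional model. The prognostic associations would be reported as descriptive only. No new data and no change in sample size are needed, and the change can be made before the unblinding planned after database freeze.

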### Inclusion criteria

Participants meeting the following criteria will be included: patients undergoing major head and neck cancer surgery (total or partial laryngectomy, crico-hyoido-epiglotto-pexy, oropharyngectomy with or without mandibulotomy, partial pharyngectomy, intraoral extended resection, extended pelvectomy, pelvi-glossectomy with or without pectoralis major flap or free flap with or without cervical lymphadenectomy) and patients receiving standardized morphine patient-controlled analgesia (PCA) in the postoperative period.

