### Non-inclusion criteria

Participants meeting one or more of the following criteria will be excluded: refusal to give consent; hypersensitivity to amide local anesthetics; hepatocellular insufficiency (international normalized ratio > 1.6) or cirrhosis; systolic heart failure (left ventricular ejection fraction < 50%); atrioventricular conduction disorders requiring permanent electrosystolic stimulation with pacemaker not yet implemented; treatment with antiarrhythmic or beta-blockers classified by Vaughan Williams; body mass index > 30 kg.m^− 2^; patient already treated for chronic pain with a level 3 analgesic or for neuropathic pain; epilepsy not controlled by treatment; acute porphyria; fluid overload; hypersensitivity to any component of 5% glucose solution; pregnant or lactating women; and patient under legal protection measure.

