### Randomization

Patients will be allocated by randomized complete block design, stratified by center, to one of the two groups that will receive either intravenous lidocaine (study group) or placebo (placebo group) during the intraoperative and early postoperative period. The randomization will be processed by the investigator after the preoperative assessment, using a computer-generated list. Allocation concealment will be transmitted to the data manager and to each pharmacy department. Allocation will be ensured by enclosing the treatment unit in sealed, opaque, sequentially numbered envelopes prepared by the pharmacy department, which will be opened only upon arrival of the patient in the operation room by a nurse who will prepare the syringes. The nurse will prepare the treatment unit away from the operating room in order to keep the study participants blinded from the allocation. Preparations will consist of two 50-ml syringes for continuous infusion by syringe pump. Postoperative outcomes will be assessed by research personnel who will remain blinded to the type of intervention throughout the study.

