### Induction and maintenance of anesthesia

After preoxygenation, anesthesia will be induced by a bolus injection of propofol and an intravenous infusion of remifentanil (Minto model for remifentanil target-controlled infusion adapted to arterial pressure and heart rate variations). Tracheal intubation may be facilitated with a neuromuscular blocking agent according to the clinicians’ decision. Patients will be mechanically ventilated with a mixture of air, oxygen, and sevoflurane. It may be noted that antihyperalgesic agents, such as nitric oxide, ketamine, or nonsteroidal anti-inflammatory drugs, are not allowed during the protocol [21–23]. In all patients, standard monitoring will be applied, including electrocardiogram, pulse oximetry, capnography, and temperature measurements.

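### Intraoperative remifentanil is compared as a cumulative total by an unadjusted t test across operations of very different extent: valid, but probably imprecise

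*Protocol article*

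**What the plan says.** Under Secondary outcome, the first item listed is "cumulative remifentanil consumption during surgery". No unit is given. Under Data analysis, "intraoperative remifentanil consumption as well as morphine consumption in the 24 postoperative hours will be compared between the two groups" with Student's t test. Neither section divides the total by operating time or adds a covariate.

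Other sections bear on this choice:

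- **Delivery.** Remifentanil is given by the "Minto model for remifentanil target-controlled infusion adapted to arterial pressure and heart rate variations" (Induction and maintenance of anesthesia).
- **Operations.** Inclusion criteria admit "total or partial laryngectomy, crico-hyoido-epiglotto-pexy, oropharyngectomy with or without mandibulotomy" and, at the larger end, "pelvi-glossectomy with or without pectoralis major flap or free flap with or without cervical lymphadenectomy". The Protocol amendment section confirms that total laryngectomy, free-flap coverage and women were added in October 2016.
- **Allocation.** "Patients will be allocated by randomized complete block design, stratified by center, to one of the two groups" (Randomization). Neither procedure nor flap is a stratification factor.
- **Where duration is used.** Type and duration of surgery are candidate factors in the regression for 48 h morphine. They are not mentioned for remifentanil.
- **Subgroups.** Data analysis and Limits plan an analysis by flap status, without saying for which outcomes.

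**The concern.** The two morphine outcomes are totals over fixed windows of 24 h and 48 h. Remifentanil is the only consumption outcome whose window differs from patient to patient: its total is the requirement per unit time multiplied by the time the infusion ran. If lidocaine spares opioid during surgery, the effect should appear in the requirement. Differences in operating time between a partial laryngectomy and a free-flap reconstruction add spread that has nothing to do with treatment.

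The protocol names the mix of procedures as a limitation and offers duration as an explanatory factor for morphine, yet makes no use of it where it multiplies the outcome directly. What is at stake is precision. A moderate remifentanil effect could be missed or estimated with a wide interval, and an uneven share of long operations could make the single observed difference hard to interpret.

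**Working it through.** **The plan's own figure.** None is given for remifentanil: no mean, SD, duration or weight distribution. The only sample-size figure is for 48 h morphine (20% of 43 mg = 8.6 mg, SD 17 mg, power 0.80, 57 per group, 64 after 10% dropout). Those inputs give 62 per group by the normal formula and 63 by the t test, two-sided 5%. That is a separate matter. Here 57 is used simply as the plan's number per group.

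**Inputs.**
- From the protocol: 57 per group, Student's t test, significance level 0.05 (two-sided assumed).
- Borrowed from the primary outcome: a 20% reduction, with 10% and 30% on either side.
- Assumed, because the protocol is silent: CV of rate per kg 0.3–0.4, of weight 0.15–0.20, of duration 0.2–0.5, mutually independent and lognormal.

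**Formulas.**
- Total = rate × weight × duration, so CV_total = √[(1 + CV_rate²)(1 + CV_weight²)(1 + CV_duration²) − 1].
- With control mean 1 and treated mean 1 − r, the average SD is s = CV × √[(1 + (1 − r)²)/2] and the standardized effect is r/s. Power comes from the noncentral t distribution.

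**Two ends of the range for r = 0.20,** where √[(1 + 0.64)/2] = 0.906:
- Rate 0.3, weight 0.15, duration 0.2: CV_total = √(1.09 × 1.0225 × 1.04 − 1) = 0.399; effect 0.20/(0.399 × 0.906) = 0.554; power 0.83.
- Rate 0.4, weight 0.20, duration 0.5: CV_total = √(1.16 × 1.04 × 1.25 − 1) = 0.713; effect 0.310; power 0.38.
- Dose per kg per hour leaves only the rate CV: 0.3 gives effect 0.736 and power 0.97; 0.4 gives 0.552 and 0.83.

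**Power with 57 per group, over the whole grid.**

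| True reduction | Raw total | Dose per kg per hour |
|---|---|---|
| 10% | 0.12–0.29 | 0.29–0.46 |
| 20% | 0.38–0.83 | 0.83–0.97 |
| 30% | 0.73–0.996 | at least 0.996 |

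The two ranges meet only because they pool two rate CVs. Like for like at a 20% reduction, rate CV 0.3 gives 0.44–0.83 against 0.97, and rate CV 0.4 gives 0.38–0.68 against 0.83. Weight and duration supply 29% to 75% of the log-variance of the raw total.

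**Does it depend on weight?** If the unstated unit is already per kg, drop the weight term. CV_total is then √(1.09 × 1.04 − 1) = 0.366 to √(1.16 × 1.25 − 1) = 0.671, and power for 20% is 0.89 to 0.41. Most of the loss comes from duration.

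**Does it depend on 57?** Few patients should drop out of an intraoperative measure, so 64 per group may be closer. Power for 20% is then 0.41–0.88 (raw total) against 0.87–0.99 (per kg per hour).

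**Validity.** In simulation (5,000 replicates in each of four CV combinations), the raw comparison had type I error 0.049–0.054. A true 20% reduction was recovered with mean difference −0.199 to −0.202. There is neither bias nor inflated error.

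**Chance imbalance.** With 57 per group, the 95% limits for the between-arm difference in mean duration are about ±1.96 × CV × √(2/57): 7% for CV 0.2, 11% for 0.3 and 18% for 0.5.

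**The case against.** The strongest reply is that an unadjusted comparison of a randomized outcome is valid. Randomization balances duration and weight in expectation, and the standard error already carries any chance imbalance. The simulation confirms this, and the reply stands in full. A reader might infer that the t test mostly compares how long the operations lasted, or that duration and weight drown any lidocaine effect. The documents do not support either reading. They give no spread for remifentanil, duration or weight, and under the assumed values a 30% reduction is still found with power of at least 0.73.

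The weight element is also weaker than the duration element. No unit is stated, a total per kg would fit the wording, and non-inclusion of "body mass index > 30 kg.m^− 2" narrows the spread.

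The total is a meaningful quantity in its own right. The hypothesis is opioid sparing, and the Background links high opioid doses to hyperalgesia and chronic pain. Replacing the total with a rate would change the question, so it should be kept.

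Two replies carry less weight. One is that a condensed article leaves such detail to an analysis plan. That covers the unit, but the article does state both the quantity and the test. The other is that the flap subgroup analysis deals with the mix of procedures. It does not sharpen the overall comparison, and durations still vary within each subgroup.

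**Conclusion.** The point holds as one of efficiency on a secondary outcome. The stated analysis gives a valid, unbiased answer but may give up substantial precision: at a 20% reduction, power of roughly 0.4–0.8 where about 0.8–0.97 is attainable on the dose-per-kg-per-hour scale. These figures rest on assumed CVs, on independence of rate, weight and duration, and on lidocaine not changing operating time. If infusion rates tend to be lower in long operations, the raw total varies less than assumed and the loss is smaller. If they tend to be higher, the loss is larger.

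The higher power belongs to the duration-normalized analysis. The gain from adjusting the total for center and planned flap depends on how much of the variance these explain, which the protocol does not allow one to compute. The primary outcome and the conduct of the trial are not affected.

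**What to change.** 1. Keep cumulative remifentanil as the stated outcome and give its unit. Compare it in a linear model with treatment, center and planned flap (yes/no), flap being the plan recorded before randomization. This model has to be written in: the regression now described is for 48 h morphine, and its listed factors include neither treatment nor center.
2. Prespecify one supporting analysis, either remifentanil per kg per hour or the total adjusted for duration and weight.
3. Define one duration and use the same window for dose and time. Remifentanil starts at induction and the study drug only at the end of induction, so duration of surgery and duration of infusion are not the same.

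**Cost.** Some wording and one extra analysis. Weight is needed for dosing by body weight, duration of surgery is already a listed factor, and flap status is needed for the planned subgroups. The protocol does not say whether the planned or the performed flap is recorded, so that should be settled. Patient care and sample size do not change. The downside is that duration is measured after randomization. The normalized result should therefore be labeled supportive, and operating time reported by arm so that readers can judge whether treatment altered it.

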## Discussion

### Benefits

Recently, intravenous lidocaine has been shown to effectively control postoperative pain according to the surgical procedure. Pain relief is reported to persist for 48 h after infusion [8]. There are no published data regarding systemic lidocaine in major head and neck cancer surgery. We hypothesized that perioperative intravenous lidocaine would lead to opioid sparing and CPSP reduction.

The benefit of lidocaine for pain relief is not likely to be due to sodium channel blockade regarding the perioperative relatively low blood concentrations [8]. It may therefore be related to a priming blockade of granulocytes, which could limit the exaggerated release of cytokines and reactive oxygen species [27], even effective at very low concentration [28].

Lidocaine is widely used intravenously in the perioperative period for abdominal and urological procedures and could lead to opioid sparing, through analgesic and anti-inflammatory properties [8]. Moreover, by an antihyperalgesic effect, systemic lidocaine could prevent CPSP [3–5]. Assessment of hyperalgesia and CPSP is permitted as we tried to limit the use of antihyperalgesic drugs (such as nitric oxide, ketamine, and nonsteroidal anti-inflammatory drugs) [21–23].

Moreover, surgery-induced stress and anesthetic-induced and opioid-induced immunosuppression during the perioperative period may play a critical role in the establishment and growth of metastatic lesions. The role of anesthetic-induced immunosuppression in the promotion of cancer recurrence is suggested by currently available preclinical studies [29] (Additional file 1).

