### Limits

The study does, however, have several limitations. One limitation is the recruitment of patients undergoing various types of procedure. Surgical techniques will be obviously different according to each procedure, and therefore we have planned subgroup analyses (with or without major pectoralis flap or free flap). Another limitation is that, for organizational issues, treatment units have to be prepared by a PACU nurse who then brings the syringe to the operating theater but who will not be involved in the care of the study patient. Although this aims to guarantee blinding, as the nurse and the medical team treating the patient will be in the same department then a bias due to unblinding cannot be ruled out. Furthermore, if use of postoperative corticosteroids was expected by the surgical team, the patient was not enrolled. However, if corticosteroids are infused in the perioperative period because of a potential upper airway edema, the patient will not be excluded; analyses conducted according to the intention-to-treat principle will be used for analysis, and sub-group analysis will be considered according to each group’s workforce.

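### The flap subgroup comparison, as worded, does not test whether the lidocaine effect differs by flap, and a possible corticosteroid subgroup would be formed after randomisation; both are subsidiary analyses and cheap to put right

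*Protocol article*

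**What the plan says.** **Flap.** Data analysis, in the protocol article, gives the flap analysis one sentence: "Subgroup analysis will be performed to compare patients with and without major pectoralis flap or free flap". Limits returns to it. After naming the variety of procedures as a limitation, it says "we have planned subgroup analyses (with or without major pectoralis flap or free flap". Neither place mentions the lidocaine-placebo contrast within or across the flap strata, and no interaction term appears in the article. The significance threshold in Data analysis is p < 0.05, with no separate provision for subgroups.

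**Corticosteroids.** Limits describes two situations. In the first, "if use of postoperative corticosteroids was expected by the surgical team, the patient was not enrolled". In the second, "if corticosteroids are infused in the perioperative period because of a potential upper airway edema, the patient will not be excluded". For the second group the article keeps to intention to treat and adds that "sub-group analysis will be considered according to each group’s workforce". Data analysis does not mention this subgroup.

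**Timing and mechanism.** The Randomization section says: "The randomization will be processed by the investigator after the preoperative assessment, using a computer-generated list". The Benefits section says that lidocaine could spare opioids "through analgesic and anti-inflammatory properties"; the Background also credits it with anti-inflammatory activity.

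**The concern.** The flap analysis has a stated purpose: to deal with heterogeneity of procedures. For a trial of lidocaine, the useful question is whether the lidocaine effect differs between patients with and without a flap. A contrast between the two kinds of patient answers another question. Separate tests in each stratum are also a poor guide, because in strata this small one test can easily reach significance and the other miss it when the true effect is the same. A reader could then be told that lidocaine works only with a flap, or only without one, on no real evidence.

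The corticosteroid subgroup raises a different problem. Its members are identified after allocation. If arm influences who receives steroids for airway oedema, lidocaine and placebo patients within that subgroup are no longer comparable by virtue of randomisation.

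**Working it through.** **Inputs.** From Sample size calculation: control mean 43 mg, SD 17 mg, 20% reduction, 57 evaluable per group (114 in total), 128 with dropout. From Data analysis: alpha 0.05. Sidedness is not stated, so two-sided is assumed. The flap share is not given, so a range is used.

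Effect: 0.20 × 43 = 8.6 mg. Standardised: 8.6 / 17 = 0.506.

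**The plan's own figure.** The normal approximation gives n per group = 2 × (17 / 8.6)² × (1.96 + 0.842)² = 61.3, so 62. The exact t test gives 62.3, so 63. The stated 57 per group does not reproduce two-sided from the printed inputs; it gives 77.1% power (normal) or 76.3% (t test). That is a separate matter. The 57 is used below only as the planned number of evaluable patients.

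**Reading 1: flap patients against no-flap patients.** Let P1 and L1 be mean morphine on placebo and lidocaine with a flap, and P0 and L0 the same without.
- Literal contrast: (P1 + L1)/2 − (P0 + L0)/2.
- Effect modification: (P1 − L1) − (P0 − L0).

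If flap surgery simply hurts more, adding the same amount to P1 and L1, the first quantity rises by that amount and the second does not move. The literal contrast therefore carries no usable information on whether lidocaine acts differently.

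**Reading 2: a separate lidocaine-placebo t test in each stratum.** Assume the same 8.6 mg effect in both. With powers p and q, the chance that exactly one test is significant is p(1 − q) + q(1 − p).

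| Per arm, two strata | Power p | Power q | Exactly one significant |
|---|---|---|---|
| 28 / 29 | 0.460 | 0.473 | 0.460 × 0.527 + 0.473 × 0.540 = 0.498 |
| 20 / 37 | 0.345 | 0.574 | 0.345 × 0.426 + 0.574 × 0.655 = 0.523 |

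An interaction test at 0.05 would signal a difference 5% of the time in this situation.

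**What an interaction test can deliver.** With a and b patients per arm with and without a flap, SE = 17 × √(2/a + 2/b). Power for an 8.6 mg difference in effect is Φ(8.6/SE − 1.96). At N = 114 the SE of the overall effect is 17 × √(4/114) = 3.18 mg.

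| Flap share | a, b per arm | SE (mg) | SE relative to overall | Power at 8.6 mg | Detectable with 80% power (mg) |
|---|---|---|---|---|---|
| 50% | 28.5, 28.5 | 6.37 | 2.0 | 27% | 17.8 |
| 30% | 17.1, 39.9 | 6.95 | 2.2 | 24% | 19.5 |
| 20% | 11.4, 45.6 | 7.96 | 2.5 | 19% | 22.3 |

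At N = 128 the powers are 30%, 26% and 21%. For 80% power at 8.6 mg the total N would be about 491, 584 and 767.

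**Corticosteroids.** No arithmetic applies. Randomisation follows the preoperative assessment. Patients with foreseen postoperative steroid use are kept out at enrolment. The steroid users who remain are therefore recognised after enrolment, and on the article's sequence allocation is already fixed. The steroids are for potential airway oedema, an inflammatory complication, and the article credits lidocaine with anti-inflammatory action. Dependence of steroid use on arm is thus possible on the trial's own reasoning, though nothing in the article shows it.

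**The case against.** The strongest reply is that the flap sentence is one line in a condensed article. Comparing the treatment effect between flap strata may be what was meant, and the model term is normally left to a statistical analysis plan, which is not shown. This stands in part: the wording may be loose, and the absence of an interaction term would not be a finding by itself. But the article does state a comparison and gives it a purpose that the comparison, as worded, does not serve.

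A reader might infer that the trial has committed to separate tests in each stratum and so carries a 50% chance of a false subgroup claim. The text does not support that. No within-stratum test is described, and the figure holds only under that assumed reading, with one-significant-one-not then interpreted as a difference in effect.

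A reader might also infer that a biased steroid analysis is planned. It is not: it is absent from Data analysis and is only to be considered under Limits, in the same sentence that keeps these patients in the intention-to-treat analysis. Making it depend on group sizes is a feasibility condition, not selection on results. Steroid use may be prophylactic and driven by the surgery, and the anaesthetist is blinded. So dependence on arm is a possibility, not a demonstrated bias.

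Finally, the interaction test is weak here. That is true, and it argues for an estimate with its interval over any significance verdict.

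**Conclusion.** The point holds as a minor one. Neither plausible reading of the flap sentence, the literal contrast or separate stratum tests, shows whether the lidocaine effect differs by flap, and an arm-by-flap term is a better method at little cost. The 50% to 52% figure rests on separate two-sided tests, an equal 8.6 mg effect in both strata, SD 17 mg, 57 per arm and an assumed flap split. The interaction estimate will be imprecise: about 19% to 27% power at N = 114 for an 8.6 mg interaction, with a flap share of 20% to 50%. A non-significant interaction would therefore not show that the effect is the same in both strata.

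The steroid subgroup, if it were run, would be defined by treatment given after randomisation and could depend on arm; it is better kept descriptive. It would be wrong to conclude that the main result is at risk: the primary t test under intention to treat and the stated secondary outcomes do not rely on either subgroup.

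**What to change.** 1. Replace the flap sentence with one linear model for 48 h morphine containing arm, centre, flap and arm × flap. Use planned flap status if it was recorded before randomisation; the article does not say whether it was, so this needs checking.
2. Report the interaction estimate with its 95% CI and the stratum-specific lidocaine effects from the same model. Label them exploratory and state that power is low.
3. Report perioperative corticosteroid use by arm descriptively, and do not use it to define an efficacy subgroup. Keep the intention-to-treat estimate as the comparison of arms.

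The cost is a few lines of wording, settled before unblinding. No extra patients are needed, and no new data beyond planned flap status if it was not captured. The primary analysis does not change.
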